### Intervention

The intervention is presented as a comprehensive dietary and lifestyle intervention called “e-PPOP” (electronic-Personalized Program for Obesity in Pregnancy), including a combination of diet, exercise, and behavior strategies available on a web-based platform specifically developed by BePatient™ according to our program requirements. The e-health platform is accessible through the web when using computer, or through an application when using tablet and smartphone. The platform includes patient’s and professional’s modules. The patient’s modules have been designed to help obese pregnant women change their lifestyle and improve their health through a personalized e-learning program (Additional file 1). The professional’s modules provide a remote follow-up of patient activities, such as questionnaires completion, self-monitoring of weight, e-learning program adherence. A social network is also available to facilitate contacts between patients and between patients and caregivers.

The individualization of the e-learning program has been essential in the development of our educational module. Personalization follows an algorithm based on participant’ answers to the initial online assessments, covering eating behavior, physical activity, diet and motivation competences (Additional file 2).

#### Patient’s module

A comprehensive e-learning module offers to participants to access a personalized lifestyle program elaborated by our multidisciplinary team, including dietician, psychologist, physical activity coach, midwife and physician. It provides educational contents, which have been elaborated according to the French guidelines for nutrition and physical activity during pregnancy [27] and evidence-based behavior-change counseling [28–31]. The objectives of the e-learning program are to limit GWG by encouraging balanced intake of carbohydrates, fat and protein; reducing high-energy foods intake (i.e. refined carbohydrates and saturated fats); increasing intake of fruits and vegetables; and, also, by encouraging physical activity practice.

The e-learning supports are composed by a total of 162 factsheets (covering behavioral messages, nutritional information on needs during pregnancy and breastfeeding, recipes), videos of exercises and yoga classes, recording of relaxation class, as well as quizzes to evaluate the progress (see supplemental table for the list of items in the program).

Lessons or motivational messages are pushed every day on the dashboard of the patients, alternatively in diet, physical activity, well-being, and motivation topics. The sending of the lessons is individualized depending of the patient’s online assessments. For instance, a patient with a high cognitive restriction or high emotional eating score first receive advices on eating behavior regulation, to improve own feelings of hunger and satiety, and then dietary advices. A patient with a low level of physical activity first receive explanations on how physical activity can benefit to her health during pregnancy, and how daily physical activity can be easily increased, and then exercise advices.

A repeat evaluation at 32 weeks (± 3 weeks) using the self-administered questionnaires help personalize the second part of lessons of the e-learning program. A final evaluation is performed during the post-partum, up to the 10th week of post-partum, to determine whether the intervention leads mothers to sustain healthy changes in dietary and physical activity behaviors.

#### Health care provider’s module

The professional modules help physicians remotely follow patient’s activities. Professional dashboard includes patient’s details (i.e. inclusion date, validation of profile, completion of questionnaires, self-monitoring of weight, expected date of delivery) and activity of connection (last connection date, progress in the e-learning program). These modules also include administration of the forum and edition of newsletters.

#### Social network

The platform proposes also various social networking possibilities. Using a pseudo, participants are able to connect with other participants and with the caregivers, through a secured instant message system, and a forum. Weekly sessions of 2 h-discussion are animated on the forum by each caregiver of the team alternatively, to stimulate the interactivity and to answer the questions on all topics of the program (motivation, well-being, nutrition, eating behaviors, physical activity, pregnancy and breastfeeding).

#### Enhancing adherence and compliance

Adherence to the intervention is enhanced through several manners. Motivational reminders are repeatedly sent by email every 3 days until the registration, every 3 days for 3 weeks until the completion of online questionnaires, every 10 days in absence of connection to the program. Participants are encouraged to self-monitor their weight. Newsletters including general information on the trial, educational messages, and seasonal topics are sent to the participants by e-mail every month and posted on the platform. Finally, the forum offers an opened discussion room to participants and caregivers in order to promote interaction. Compliance to the program is assessed by evaluating the time spent on the platform and the percentage of completeness of the e-learning program. Acceptance of the program will be assessed in the intervention group, by monthly satisfactory questionnaires.

#### Participant timeline

The intervention takes place from 22 weeks of pregnancy throughout the pregnancy and 10 weeks of post-partum. The program starts after completion of the initial online questionnaires. It is composed by 3 sessions of 10 weeks, i.e. 20 weeks during pregnancy and 10 weeks in post-partum. Finally, the participation lasts 8 months after randomization of a given subject.

### Endpoints

The primary endpoint consists of the rate of obstetrical interventions during labor and delivery, defined as caesarean section and instrumental delivery (forceps and vacuum extractor). As secondary endpoints, we include data routinely collected as part of usual antenatal and perinatal care, such as GWG (measured with a scale at each visit), gestational hypertension (defined as systolic blood pressure ≥ 140 mmHg and/or diastolic blood pressure ≥ 90 mmHg after 20 weeks), preeclampsia (defined as gestational hypertension and proteinuria ≥0.30 g/24 h), GDM (diagnosed by a 75 g-oral glucose tolerance test between 24 and 28 weeks according to the guidelines of the International Association of the Diabetes and Pregnancy Study Groups (IADPSG)). Fetal and neonatal collected outcomes, consist of premature birth (defined as birth before 37 weeks), gestational age at birth, birth weight, rate of macrosomia (defined as birth weight > 90th percentile for gestational age), Apgar score, arterial umbilical cord pH, neonatal traumatism, hyperbilirubinemia, respiratory distress syndrome (i.e. needs for oxygen) and transfer in neonatal intensive care unit. Post-natal outcomes are duration of breastfeeding, maternal weight retention and child weight at the postnatal visit (8 ± 2 weeks’ post-partum).

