**Methods:**

Electronic-Personalized Program for Obesity during Pregnancy to Improve Delivery (ePPOP-ID) is an open multicenter randomized controlled trial which will assess the efficacy of an e-health web-based platform offering a personalized lifestyle program to obese pregnant women in order to reduce the rate of labor procedures and delivery interventions in comparison to standard care. A total of 860 eligible pregnant women will be recruited in 18 centers in France between 12 and 22 weeks of gestation, randomized into the intervention or the control arm and followed until 10 weeks of postpartum.

The intervention is based on nutrition, eating behavior, physical activity, motivation and well-being advices in which personalization is central, as well as the use of a mobile/tablet application. Inputs includes data from the medical record of participants (medical history, anthropometric data), from the web platform (questionnaires on dietary habits, eating behavior, physical activity and motivation in both groups), and adherence to the program (time of connection for the intervention group only). Data are collected at inclusion, 32 weeks, delivery and 10 weeks postpartum. As primary outcome, we will use a composite endpoint score of obstetrical interventions during labor and delivery, defined as caesarean section and instrumental delivery (forceps and vacuum extractor). Secondary outcomes will consist of data routinely collected as part of usual antenatal and perinatal care, such as GWG, hypertension, preeclampsia, as well as fetal and neonatal outcomes including premature birth, gestational age at birth, birth weight, macrosomia, Apgar score, arterial umbilical cord pH, neonatal traumatism, hyperbilirubinemia, respiratory distress syndrome, transfer in neonatal intensive care unit, and neonatal adiposity. Post-natal outcomes will be duration of breastfeeding, maternal weight retention and child weight at postnatal visit.

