To our knowledge, there is no published work that studied the effect of a technologically based intervention during the pregnancy. A program was recently tested in the post-partum period. The Diabetes Prevention Program demonstrated that an intensive, face-to-face lifestyle intervention could achieve weight loss and reduce incidence of type 2 diabetes in middle-aged adults at high-risk, including women with a GDM history [25]. However, because face-to-face lifestyle intervention studies in post-partum women have had limited success [25, 26] and given the multiple barriers to face-to-face interventions, and the widespread use of the Internet, the authors adapted the Diabetes Prevention Program into a web-based lifestyle intervention using web-based technology to deliver lifestyle interventions for women with recent GDM. The study demonstrated the feasibility and efficacy of the web-based lifestyle modification program to decrease postpartum weight retention in the first postpartum year for women with recent GDM. The authors concluded that this program is at low cost to implement and has potential for broad dissemination [19]. These data suggest that a web-based program should be tested in obese pregnant women to limit GWG.

The purpose of our study is to assess the efficacy of an e-personalized program including antenatal dietary and lifestyle advices in pregnancy to reduce the rate of labor procedures and interventions in comparison to standard care. As secondary objectives, we will investigate whether the e- program may improve the health of the mothers and their newborns, compared to a control group allocated to standard care. Maternal secondary outcomes include reducing GWG, increasing the proportion of participants having a GWG within the guidelines, reducing the risk of hypertension, preeclampsia, and GDM, reducing fat and sugar intake, increasing physical activity, increasing breastfeeding and duration, reducing weight retention after childbirth. For newborns, secondary outcomes will consist of improving birth weight, reducing risk of macrosomia, trauma associated with childbirth and low Apgar score, reducing the use of phototherapy for hyperbilirubinemia, as well as reducing number of admissions to neonatal intensive care unit and number of infants with excessive weight at postnatal visit.

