### Data collection

#### Clinical variables

At inclusion visit between 12 and 22 weeks, demography, medical and family history and current pregnancy health information are collected. Anthropometric variables (weight and height) are measured; blood and urine samples are drawn. No additional follow-up visit is required, as women benefit of the usual care for pregnancy (according to the French guidelines) which consists of 7 prenatal visits and 1 post-natal visit between 6 and 10 weeks after delivery. Information is collected from maternal medical records regarding health during pregnancy including gestational hypertension, preeclampsia and GDM. All women in both groups undergo a 75 g-oral glucose tolerance test (75 g glucose oral load after a fasting period of 10 h minimum) between 24 and 28 weeks. The diagnosis of GDM is made according to the IADPSG criteria (i.e. fasting plasma glucose ≥5.1 mmol/L [0.92 g/L] and/or 1-h glucose ≥10 mmol/L [1.80 g/L] and/or 2-h glucose ≥8.5 mmol/L [1.53 g/L]). The beginning of labor and the delivery mode are collected as well as the occurrence of post-partum hemorrhage. Neonatal and postnatal outcomes include the occurrence of traumatism due to childbirth, Apgar score, umbilical cord pH, admission to neonatal unit and use of phototherapy for hyperbilirubinemia. To address the influence of the intervention on neonatal growth and adiposity, neonatal anthropometric variables (weight, length, adiposity skinfolds) are measured within the first 24 h. At the post-natal visit, maternal demographic data, health since the delivery (post-partum complications such as fever, hemorrhage, thromboembolic events) and duration of breastfeeding are obtained. Maternal anthropometric variables (weight, height) are measured. To address the safety and the impact of the intervention on child health, details regarding the health since birth is also obtained. To address the influence of the intervention on infant adiposity, infant length and weight are measured at birth.

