### Statistics

Statistical analyses will be independently performed by the Biostatistics Department of University of Lille. Data will be analyzed using the SAS software (SAS Institute Inc., Cary, NC, USA) and all statistical tests will be performed with a 2-tailed alpha risk of 0.05. A detailed statistical analysis plan will be written and finalized prior to the database lock. For each exploratory analysis, a statistical analysis plans will be provided before any data analysis. Baseline characteristics will be described for each group. Quantitative variables will be expressed as mean (± standard deviation), median (± interquartile range) and 95% confident interval. Qualitative variables will be expressed as frequencies and percentages. Normality of distribution will be assessed graphically and using the Shapiro-Wilk test. The primary analysis for primary and secondary endpoints will be conducted on the intention-to-treat principle. A secondary per-protocol analysis will be performed.

The primary endpoint (rate of delivery interventions) will be compared between the two groups using the Chi-square test. Absolute and relative risk difference (intervention vs. control) and their 95% confidence intervals will be calculated. For the secondary objectives, binary endpoints will be compared between the two groups using chi-square tests or Fisher’s exact tests when the expected cell frequency will be inferior to 5. Quantitative endpoints will be compared between the two groups using student *t* tests or Mann-Whitney U tests in case of non-normal distribution (except if a log-transformation can be applied to normalize the data). For quantitative endpoints involving repeated measures, a linear mixed model will be used. This model allows to perform an ANOVA for repeated measures taking into account the correlation between the repeated measures. The choice of the covariance in the models will be based on the AIC criteria and normality of residuals will be checked.

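### Breastfeeding duration is cut off at a single visit 6 to 10 weeks after delivery, yet the only test rule that fits it treats every value as a completed duration

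*Protocol article*

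**What the plan says.** The Background gives, among the secondary objectives, "increasing breastfeeding and duration, reducing weight retention after childbirth". The Endpoints section turns this into an outcome: "Post-natal outcomes are duration of breastfeeding, maternal weight retention and child weight at the postnatal visit", with that visit placed at 8 ± 2 weeks.

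Under Clinical variables, usual care includes "1 post-natal visit between 6 and 10 weeks after delivery", at which health since delivery and "duration of breastfeeding are obtained". The same paragraph states "No additional follow-up visit is required". The abstract confirms the end of observation: women are "randomized into the intervention or the control arm and followed until 10 weeks of postpartum".

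The Statistics section sorts secondary endpoints by variable type. Binary ones go to chi-square or Fisher tests, repeated quantitative measures go to a linear mixed model, and for the rest: "Quantitative endpoints will be compared between the two groups using student *t* tests or Mann-Whitney U tests in case of non-normal distribution". No time-to-event method appears, and no restricted definition of the endpoint, such as status at a fixed week.

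**The concern.** A woman who stopped before the visit has a known duration. A woman still breastfeeding has only a minimum, equal to the time from delivery to her appointment. Two such women, seen at 6 and at 10 weeks, would enter a t or Mann-Whitney test with values four weeks apart, although the data say nothing about which of them breastfed longer.

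Two things are at stake for a stated secondary objective. First, differences between appointment dates are added as noise, so power is lost. Second, the recorded value depends on visit timing. The trial is open and the visit window is four weeks wide. If one arm tended to be seen later, its recorded durations would be longer with no true difference.

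**Working it through.** **1. The plan's own figures.** The document gives no figure for breastfeeding. Its sample size concerns the primary endpoint and reproduces: 50% against 40%, two-sided 5%, 80% power gives 388 per arm (387 stated), and 774 / 0.90 = 860, or 430 per arm.

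**2. Which rule applies.** A duration recorded once is neither binary nor repeated. Of the three rules in the Statistics section, only the t or Mann-Whitney rule remains.

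**3. Assumed inputs (none in the document).** 35% never start. Among starters, durations are exponential with a median of 12 or 8 weeks in controls. The hazard ratio for stopping is 0.75. Visits are uniform over 6 to 10 weeks, with 430 per arm.

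**4. Share censored.** With λ = ln 2 / median, the share still breastfeeding at the visit is 0.65 × (e^(−6λ) − e^(−10λ)) / (4λ), with 0.75λ in the intervention arm.
- Median 12: 0.65 × 0.631 = 41% (control) and 0.65 × 0.708 = 46% (intervention).
- Median 8: 0.65 × 0.503 = 33% and 0.65 × 0.596 = 39%.

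**5. Power by simulation** (recorded value = the smaller of true duration and visit time; never-starters = 0):

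| Analysis | Median 12 | Median 8 |
|---|---|---|
| t test | 17% | 24% |
| Mann-Whitney | 14% | 20% |
| Log-rank, censored at visit | 29% | 39% |
| Proportion breastfeeding at 6 weeks | 25% | 35% |

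Repeat runs agree within about two points. A hand check of the last row:
- Median 12: the proportions are 0.65 × 0.5^0.5 = 0.460 and 0.65 × 0.5^0.375 = 0.501. The standard error is √(2 × 0.480 × 0.520 / 430) = 0.034, so power ≈ Φ(0.0416/0.0341 − 1.96) = 23%.
- Median 8: 0.386 and 0.440 give Φ(0.0536/0.0336 − 1.96) = 36%.

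**6. Other assumptions.** With 387 per arm, all women starting, hazard ratio 0.75, and 30%, 50% or 70% of controls still breastfeeding at 8 weeks, power (t / Mann-Whitney / log-rank) is 82/82/88%, 64/63/75% and 38/31/54%. The loss against log-rank runs from about 5 to 24 points.

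**7. Type I error.** With no effect and equal visit timing, all three tests reject in 4.6–6.5% of runs. With no effect but visits in one arm half a week later (median 12), the t test rejects in 13% and Mann-Whitney in 22%. Log-rank and the 6-week proportion stay at about 5%. With a one-week shift the planned tests reject in 32% and 56%. Mann-Whitney suffers more because the visit date alone sets the ranking of the women still breastfeeding.

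**The case against.** The strongest reply is that the Statistics section never names this endpoint. It gives generic rules and promises a detailed analysis plan before database lock, which is where a rule for women still breastfeeding would normally sit. This stands in part: the assignment is inferred. But the section does not leave the test open. It gives a rule for quantitative endpoints, and an analysis plan with a censoring rule would have to depart from it.

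Three stronger readings are tempting, and the document does not support them.

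- *The test hides most of the effect.* At a median of 12 weeks the true difference in means is 0.65 × (12 / ln 2) × (1/0.75 − 1) = 3.8 weeks, against about 0.24 in the recorded means. A reader might blame the test. The gap arises mostly because follow-up ends at 10 weeks, and no analysis of such data recovers 3.8 weeks without extrapolation.
- *The test is invalid.* With equal visit timing it is not. Visits follow usual care in both arms, and nothing in the document suggests a shift; the shift in step 7 is hypothetical. The recorded mean can still be read as weeks breastfed up to the visit.
- *The necessary data are not collected.* The eCRF is not shown, so it cannot be said to lack a stop date or a current-status field.

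It is also fair to say that the size of the loss rests on assumed breastfeeding rates, and that even log-rank has low power in the scenarios of step 5.

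**Conclusion.** The point holds as an inefficient and fragile analysis of one secondary endpoint. It needs only that some women are still breastfeeding at 6 to 10 weeks. Under the main assumptions, the planned tests have about 14–24% power, log-rank 29–39% and the 6-week proportion 25–35%; these figures show direction and rough size and do not predict this trial's power. Bias is conditional on visit timing that differs by arm, against which the planned tests have no protection and the two alternatives do. The primary analysis and the sample size are untouched. The change should be made, but the trial's main conclusion does not depend on it.

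**What to change.** In the analysis plan, do one or both of the following:

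- Analyse time to stopping breastfeeding, censored at the visit date for women still breastfeeding, with never-starters counted as stopping at time 0. Show Kaplan-Meier curves and use a log-rank test stratified by centre, in line with the randomisation.
- Compare the proportion still breastfeeding at 6 weeks by chi-square test. With visits inside the planned window, this status is known for every woman seen.

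Two options should not be relied on. Mean duration restricted to 6 weeks does no better than the planned tests (12% and 18% power under the same assumptions). A single Cox hazard ratio that includes the time-0 events is hard to interpret, because an effect on stopping alone does not give a constant ratio when 35% of women are tied at zero.

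Confirm that the eCRF captures the stop date or a still-breastfeeding status, together with the visit date. Without these, censored and complete durations cannot be reliably separated later. The cost is wording in the analysis plan and, if the items are absent, a small eCRF change. No extra visits or participants are needed.

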### Sample size

As mentioned, the main objective of this study is to demonstrate the superiority of an electronic-personalized program over standard care to reduce the rate of delivery interventions (defined as caesarean section and instrumental (vacuum extractor and forceps) extractions) in obese pregnant women. In the AUDIPOG database of the French maternities, the rate of delivery interventions is 50% among obese pregnant women. We assumed that our electronic-personalized program could reduce this rate to 40% (i.e. a relative risk reduction of 20%). To detect this difference, using a 2-sided Chi-square test with an alpha risk of 5% and a power of 80%, we calculated that a total of 774 subjects (i.e. 387 subjects in each group) would be required (computation made using the PASS 12). Considering a maximum of 10% of drop outs or missing data, we will recruit 860 patients.

